### Interventions

2.7

All patients in 3 + PRN group will receive a minimum of 3 initial monthly IVC (0.5 mg) injection, PRN dosing thereafter BCVA and CST stabilization criteria-driven PRN treatment while 6 + PRN group will receive a minimum of 6 initial monthly IVC (0.5 mg) injection, PRN dosing thereafter BCVA and CST stabilization criteria-driven PRN treatment.

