### Sample size

2.10

This study is powered to demonstrate non-inferiority of 6 + PRN with respect to the effective rate (at 48 weeks). The trial will have sufficient statistical power to determine superiority of 6 + PRN treatment over the 3 + PRN. According to our clinical application, we initially expect the effective rate of IVC for DME to be around 75%. After calculation, 50 cases are required for each group. Considering the shedding rate of 20%, 60 cases are required for each group, and a total of 120 cases for the 2 groups.

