### Statistical analysis

2.11

SPSS statistical software (IBM Statistics, v. 22.0; IBM Corp, Armonk, NY) will be used to conduct analysis. Quantitative data, BCVA, is represented by median (quartile), and other data is represented by mean and SD. The comparison of clinical features between groups was performed using the *t* test. Changes in BCVA before and after treatment were tested using Wilcoxon–Matt–Whitney test. The change of CST and indicators of retinal blood flow from baseline were analyzed by paired *t* test. The comparison of different follow-up time indicators was performed by repeated measurement data analysis of variance. Statistical significance will be based on 2-sided tests, with *P* value less than .05 taken as the criterion for statisticalsignificance.

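### The only longitudinal method named, repeated-measures ANOVA, in its classical form uses only patients with every visit, although the plan expects 20% loss; a mixed model would use all visits collected

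*Protocol article*

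**What the plan says.** Section 2.11 of the protocol article (Statistical analysis) assigns methods by type of comparison:

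- between-group comparison of clinical features: t test;
- change in BCVA: a Wilcoxon/Mann-Whitney type test, with BCVA summarised by median and quartiles;
- change in CST and retinal blood flow from baseline: paired t test;
- comparison over follow-up times: "The comparison of different follow-up time indicators was performed by repeated measurement data analysis of variance".

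The last sentence names no outcome and no between-arm term. The software is fixed ("SPSS statistical software (IBM Statistics, v. 22.0; IBM Corp, Armonk, NY) will be used to conduct analysis"), but no procedure within it is named.

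Section 2.10 (Sample size) states "After calculation, 50 cases are required for each group" and continues "Considering the shedding rate of 20%, 60 cases are required for each group, and a total of 120 cases for the 2 groups". Section 2.8.1 places BCVA and CST at baseline and months 1, 3, 6 and 12. Section 2.5.1 makes mean change in BCVA at 24 and 48 weeks the primary outcome. In section 2.7 the arms differ in the length of the loading phase: at least three monthly injections in the control arm, whereas "6 + PRN group will receive a minimum of 6 initial monthly IVC (0.5 mg) injection".

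**The concern.** Classical repeated-measures ANOVA needs a full row of visits for each patient. A patient seen at baseline and months 1, 3 and 6 and then lost contributes nothing, although four values were collected. A plan that expects one patient in five to leave has therefore chosen a longitudinal method that fits its own expectation badly.

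Two things are at stake. The first is information: data already collected are thrown away, including month-6 values that bear on the 24-week outcome. The second is validity. If leaving is related to how the eye is doing, the patients who remain do not represent those randomised, and the change over time is distorted. If the amount of leaving, or its relation to outcome, also differs between arms, any arm contrast taken from the ANOVA is distorted too. The arms differ in the number of obligatory monthly injections, so different reasons for leaving are conceivable, though nothing in the article shows that they will occur.

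**Working it through.** **The plan's own figure.** Inputs from section 2.10: 50 per arm required, 20% loss, 60 per arm recruited.

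- 50 × (1 + 0.20) = 60. This reproduces the stated number.
- The usual allowance is n/(1 − d) = 50/0.80 = 62.5, so 63 per arm (126 in total).

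The 50 itself cannot be checked, because the article gives no margin, power or arm difference.

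**Patients left in a complete-case ANOVA.**

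- Expected loss only: 60 × 0.80 = 48 per arm, 96 of 120 in total, against 50 required per arm.
- If those who stay also miss each of the four post-baseline visits independently (assumed rates): at 2% per visit, 48 × 0.98⁴ ≈ 44; at 5%, 48 × 0.95⁴ ≈ 39.

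**What is lost at week 24.** Take month 6 as the week-24 visit and suppose all 12 losses per arm come after it. Then 60 per arm have a month-6 value and the ANOVA uses 48. For an arm difference at that visit the variance rises by the factor 60/48 = 1.25.

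**Possible bias.** No SD, correlation or dropout mechanism is given in the article, so two illustrative simulations with assumed values were run. Neither has a true arm difference. Differences are 6+PRN minus 3+PRN at month 12, in letters.

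Simulation A: 400,000 patients per arm; SD 10; correlation 0.6; true month-12 change 8 in both arms; about 20% leave after month 6; log-odds of leaving change by 0.1 per letter of month-6 change.

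| Dropout | Completers, 3+PRN | Completers, 6+PRN | Difference, completers | Difference, all visits (missing at random) |
|---|---|---|---|---|
| Random | 7.99 | 7.98 | −0.01 | −0.02 |
| Poor responders leave, alike in both arms | 9.06 | 9.03 | −0.03 | −0.02 |
| Poor leave 3+PRN, good leave 6+PRN | 9.08 | 6.92 | −2.16 | −0.01 |

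The second row matters for the quoted sentence read literally. The arm difference is unbiased, but each arm's change is about 1 letter too high (9.06 − 8 = 1.06; 9.03 − 8 = 1.03).

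Simulation B: 3,000 trials of 60 per arm; SD of change 9; visit correlations 0.55 to 0.75; about 20% dropout by month 12 except where shown; log-odds of leaving change by 1 per SD of the last observed change.

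| Dropout | Difference, completers | Difference, likelihood on all visits |
|---|---|---|
| Random | 0.03 (SE 1.86) | 0.03 (SE 1.77) |
| Poor responders leave 6+PRN only | 1.26 | 0.00 |
| Poor leave 3+PRN, good leave 6+PRN | −2.50 | 0.00 |
| Poor responders leave, about 15% v 29% | 0.75 | 0.01 |

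Under random dropout the completers' variance is (1.86/1.77)² ≈ 1.10 times that of the all-visits estimate. The near-zero bias of the all-visits estimates follows from the set-up, because dropout was made to depend on observed values. It shows what the method does when missing-at-random holds, not that it holds here.

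**The case against.** The strongest reply is that the quoted sentence does not define the arm comparison. It concerns follow-up times and has no arm term. The tests listed for BCVA change and for group features need only the values they use, so a missed month-1 or month-3 visit would not remove a patient from a week-48 test. This stands. A reader might infer that the trial's arm comparison becomes completers-only because of the ANOVA; section 2.11 does not say so. A patient lost before month 12 would, without imputation, also be absent from a month-12 rank or t test, but that is missing-data handling in general, which an article commonly leaves to a fuller document.

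Three other tempting readings fail:

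- Recruiting 60 to allow for loss does not show that a completers analysis is intended. Such inflation is routine whatever the analysis set.
- Dropping incomplete patients is the classical method's behaviour, not the article's text. No imputation is stated, and none is ruled out.
- Unequally spaced visits might suggest that a sphericity assumption will fail unaddressed. Standard corrections exist, and the article does not say they will be omitted.

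It is also fair to say that the simulated biases rest on assumed inputs. The largest needs poor responders to leave one arm and good responders the other, which nothing in the article suggests, and the biases of 0.75 and 1.26 letters are smaller than the standard error of about 1.8.

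What remains is a choice that the article does state: its single longitudinal method is one that, in classical form, makes poor use of incomplete follow-up, in a plan that predicts incomplete follow-up.

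**Conclusion.** The point holds in a limited form. Classical repeated-measures ANOVA without imputation would rest on about 48 of 60 patients per arm, below the 50 required, and on about 44 or 39 under the assumed rates of isolated missed visits. That count follows from the plan's own figures, provided the classical complete-case procedure is the one meant.

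Bias is possible, not established. The change over time is affected if dropout relates to outcome. An arm contrast taken from the ANOVA is affected only if the amount of dropout or its link to outcome differs by arm: about 0 letters when dropout is random or acts alike in both arms, and about −2.2 to −2.5 letters in the opposite-direction scenarios. These values illustrate the mechanism and are not forecasts. The change should be made, because a better method is available at little cost, but the documents do not show that the primary comparison is biased as written.

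**What to change.** In section 2.11, replace repeated-measures ANOVA with a mixed model for repeated measures: SPSS MIXED, unstructured covariance, with arm, visit, arm-by-visit, baseline value and baseline-by-visit. Include all randomised patients with any post-baseline value, analysed in the arm to which they were randomised. Report the week-24 and week-48 arm contrasts with 95% confidence intervals. Keep the rank-based BCVA test as a sensitivity analysis.

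Cost: no new data and no new software, since the model is in the package already named. It is more than rewording one sentence, however, because taking the BCVA contrasts from the model moves the primary analysis away from the rank-based test, and that should be stated openly. The model relies on missing-at-random and on approximately normal residuals; the first is a weaker assumption than a completers analysis needs. The Discussion reports 28 eyes recruited by July 6, 2020, so at the time of writing the change could still be made early in recruitment.

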## Discussion

3

Currently, this will be the first study to evaluate the effectiveness and safety of 6 + PRN regimen IVC compared with 3 + PRN regimen. Progress made so far (till July 6, 2020): recruitment has started at all participating sites (n=7). To date, a total of 28 eyes have been recruited into the trial.
